## Results

The project was funded in April 2016 and enrolment is on-going. The first results are expected to be submitted for publication in 2020. Study measures are assessed at baseline, immediate posttest following training, and at 2 annual follow-ups. These assessments are categorized by: (1) demographic, background, and covariate measures; (2) Aim 1, neurocognitive measures; (3) Aim 2, everyday functioning measures; (4) Aim 3, quality of life measures (see Table 1). Most of these measures use standardized instruments that have good to excellent psychometric properties; this is particularly relevant for the neurocognitive assessments as they are used to determine HAND [12,55,110-118].

**Table 1 table1:** General domains assessed overtime.

Demographic, background, and covariate measures	Aim 1: Neurocognitive measures	Aim 2: Everyday functioning measures	Aim 3: Quality of life measures
Demographic questionnaire Wide range achivement test- 4 (Educational quality) [119] Drug urine screen HIV history and status Electronic medical records	Speed of processing (ie, UFOV^b^) [120] Attention and working memory (PASAT^a^-2000) [121] Learning ie, Hopkins verbal learning test- Revised) [115,116,122] Verbal memory (ie, Hopkins verbal learning test- Revised) [115,116,122] Verbal fluency (ie, controlled oral work association test) [123] Executive function (ie, Wisconscin card sorting test) Psychomotor (ie, grooved pegboard) Reported instrumental activities of daily living (IADLs) (ie, Lawton & Brody activities of daily living questionnaire)	Driving simulator [13,82,107] Driving habits questionnaire [124] Retrospective & prospective state crash records [125] Timed instrumental activities of daily living [126,127] Medication aherence	Centers for epidemiological studies- Depression (CES-D) [128,129] Internal locus of control [85] Self-rated health and health related quality of life (measured via medical outcomes study short-form (SF-36) [130] Neurocognitive Complaints

^a^PASAT: Paced auditory serial attention test.

^b^UFOV: Useful field of view.

One primary and novel focal area of this study (Aim 2) is driving and driving-related outcomes. Most adults with HIV experience some degree of neurocognitive impairment, and coupled with the lack of adequate public transportation or social support, many adults must rely on their own driving and navigational skills to carry out basic IADLs such as grocery shopping and visiting their medical providers. Thus, this cognitive intervention is expected to benefit such driving outcomes [77,131-135].

Driving is assessed in 3 primary ways: (1) driving simulation, (2) the driving habits questionnaire, and (3) retrospective and prospective state crash records [124]. As mentioned earlier, the driving simulator has been used in earlier studies to document the relationship between functioning in certain neurocognitive domains on particular driving simulator outcomes [13]. Such standardized, performance-based outcomes include: average gross reaction time, percentage of time driving outside of the lane, percentage of time driving over the posted speed limit, and so on.

The driving habits questionnaire [124] is a self-report survey that assesses driving exposure and driving avoidance across varying difficult driving circumstances (eg, driving at night). Driving exposure [124] is assessed with 4 self-reported items: (1) number of days per week driven (0–7), (2) miles driven per week (numeric estimate), (3) miles driven per year (estimated to the nearest 2500 miles), and (4) driving space (the further one has driven from home in the past year). These items can then be standardized (*z*-scored) and summed to form a driving exposure composite score.

Driving avoidance [124] is assessed with 10 self-reported items that ascertain whether participants passed up opportunities to drive in the past 3-month period due to avoiding difficult driving circumstances: (1) driving at night, (2) driving in bad weather, (3) driving alone, (4) driving on interstate highways or expressways, (5) driving in unfamilar places, (6) driving on high traffic roads not including interstates, (7) driving in rush-hour traffic, (8) making lane changes, (9) making left-hand turns across oncoming traffic, and (10) merging into traffic while entering a highway or expressway. Likewise, these items can then be standardized (*z*-scored) and summed to form a driving exposure composite score.

Retrospective and prospective vehicle state crash records are also accessed through the Alabama Department of Transportation (ADOT). As in past studies, using participants’ driver’s license numbers, a request is made to the ADOT office requesting for accident reports which are publically available records and made available for a small fee. These files contain police reports that describe the circumstances of the accident. Based upon these reports, a determination of whether participants were at fault or not is determined by 2 independent raters; when there is a lack of an agreement, a third rater makes the final determination. Thus, these state crash records can be used to determine what variables are correlated to the number of total crashes, number of at-fault crashes, and number of not-at-fault crashes. The use of actual, real life vehicle crash records provides convergent validity to the other driving measures and is also ecologically valid.

Crash records can be examined both retrospectively and prospectively. Retrospectively, once the entire initial sample’s baseline data are collected, participants’ driving records can be requested for the 5 years prior to starting our study and examined to determine crash rates and neurocognitive predictors of crashes. Prospectively, once participants have completed the training in our 2-year study, it can be determined through logistic regression and hierarchical regression whether this intervention was effective in reducing the frequency and severity of vehicle crashes. Given the infrequent nature of vehicular crashes, the large sample size of this study will provide insight into whether this intervention is effective in helping adults with HAND maintain safe driving. Although obtaining information on participants’ driving exposure and driving avoidance may modify the risk of crashes for some of our participants, their combined influence can be examined over time as these variables are assessed at each time point.

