#### Inclusion Criteria

Since driving-related factors are being examined as 1 of the outcomes of the intervention, participants must be licensed drivers when entering the study. Otherwise, participants (men and women) must be 40+ years, English-speaking, and have HAND.

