#### Exclusion Criteria

Due to this study being longitudinal, participants not living in stable housing (eg, halfway house) are excluded because of the challenge of scheduling follow-up visits. Potential participants are excluded if they indicate that they are planning to move away from the Birmingham metropolitan area within the next 2 years. Furthermore, participants with significant neuromedical comorbidities (eg, schizophrenia, epilepsy, bipolar disorder, multiple sclerosis, Alzheimer disease or related dementias, mental retardation) are excluded; such major neurological comorbidities may confound study results and interfere with the cognitive training. These comorbidities are assessed in the telephone screen and confirmed after the baseline assessment using the university HIV and AIDS Clinic electronic medical charts. Other conditions (eg, legally blind or deaf [vision confirmed at baseline], currently undergoing radiation or chemotherapy, a history of brain trauma with a loss of consciousness greater than 30 minutes) that could impact neurocognitive functioning or testing also necessitates exclusion; again, this information is conferred in the telephone screen and again at baseline. These typical exclusion criteria are used in many HIV neurocognitive studies [12,14,101-104]; we wish to exclude those with other major neurological conditions besides HIV that affect neurocognition.

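### The 5-year look-back for crashes uses one state's records, but nothing in eligibility or the exposure measures secures or measures 5 years of observable time in that state

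*Protocol article*

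**What the plan says.** All of this is in the protocol article.

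- **Source (Results, state crash records).** Crash records come from the Alabama Department of Transportation and are sought by driver's licence number: "a request is made to the ADOT office requesting for accident reports which are publically available records". No other state is named.
- **Window and purpose (same place).** Once baseline data on the whole initial sample are in, "driving records can be requested for the 5 years prior to starting our study and examined to determine crash rates", along with which neurocognitive measures predict crashes.
- **Form of the variable (same place).** The records are to yield "number of total crashes, number of at-fault crashes, and number of not-at-fault crashes". No person-time denominator is given.
- **Licence (Inclusion Criteria).** "participants must be licensed drivers when entering the study". Neither a state of issue nor a minimum duration is stated.
- **Residence (Exclusion Criteria).** People are excluded if they are "planning to move away from the Birmingham metropolitan area within the next 2 years". No criterion concerns past residence.
- **Exposure (Results, driving habits questionnaire).** Exposure is asked per week or per year and avoidance over the last 3 months, at each study visit. The crash section names these two measures as possible modifiers of crash risk.

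**The concern.** The criteria protect 2 years of observation forward, whereas the retrospective analysis needs 5 years of observation backward. In a single state's file, an empty record can mean that the person had no crash or that the person could not have been seen there. Nothing described in the article separates the two.

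Two groups are affected in different ways. Someone who moved to Alabama during the window may have had crashes elsewhere that the request does not return. Someone who lived in Alabama but gained or regained a licence during the window was mainly at lower risk beforehand. That person's zero may be true, but dividing by 5 years would still give too low a rate per year at risk.

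At stake are the baseline crash rates and the analysis of neurocognitive predictors of past crashes. The article lists crash records as one of three primary ways of assessing driving and relies on them for convergent and ecological validity. It also calls crashes infrequent, so false zeros would be hard to notice among true ones.

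**Working it through.** **Is there a stated figure to reproduce?** No. The article gives no crash rate, event count or power for this outcome. It also gives no share of participants with an incomplete look-back. What follows is illustration under stated assumptions.

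**Time needed against time secured**

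| Item | Period covered |
|---|---|
| Retrospective crash window | 5 years before entry |
| Licence criterion | day of entry |
| Residence criterion | 2 years after entry |
| Exposure items | at most the past year |
| Avoidance items | past 3 months |

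No row below the first covers years 2 to 5 before entry.

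**One affected person.** With a constant crash rate, the expected recorded count as a fraction of the full-window count is m/5, where m is the number of observable years.

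- m = 1: 0.20
- m = 2: 0.40
- m = 2.5: 0.50
- m = 4: 0.80

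**Whole sample.** Let f be the share with an incomplete look-back and m their mean observable years, with the same crash rate in everyone. If a fixed 5-year denominator were used:

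recorded rate / true rate = [(1 − f) × 5 + f × m] / 5, so the understatement is f × (1 − m/5).

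| f (assumed) | m = 1 | m = 2.5 | m = 4 |
|---|---|---|---|
| 5% | 4% | 2.5% | 1% |
| 10% | 8% | 5% | 2% |
| 20% | 16% | 10% | 4% |
| 30% | 24% | 15% | 6% |

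The 5-15% illustration is the m = 2.5 column for f from 10% to 30%. The full grid runs from 1% to 24%.

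**Link with cognition.** If f and m are the same at every level of cognition, the shortfall cancels from a rate ratio and only events are lost. If they differ, the ratio is multiplied by the ratio of the two recorded fractions. For example, with m = 2.5 throughout and f = 30% in one cognitive group against 10% in the other, the factor is 0.85 / 0.95 = 0.89. A true ratio of 1 would then appear as 0.89. Nothing in the article shows whether residence or licence history differs by cognition.

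**The case against.** The strongest objection is that the article never says how incomplete look-back is handled. It speaks of rates, and a rate implies a denominator. It does not fix that denominator at 5 years and does not rule out person-time. A condensed article may leave such detail to a full protocol or analysis plan. This stands to the extent that one cannot say newcomers are recorded as crash-free. A reader might infer that from the uniform window and the counts, but no sentence states it. The objection does not dispose of the point. Person-time can be used only if residence and licence dates are collected, and the article's own exposure measures do not supply them for the look-back.

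A second objection is that the affected group may be small. Participants are aged 40 or over, in stable housing, recruited at one local clinic, and not planning to move away. That makes the low end of the range plausible, but the document does not settle it.

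A third is that the licence rule is a reasoned choice, because driving is a trial outcome and licensed drivers are the intended population. This stands. A reader might go further and call the sample selected on its own outcome, since some people may have lost a licence through crashes. The article offers no evidence of that, and a plain statement of the population described is enough.

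Finally, a reader might conclude that the treatment effect on crashes is biased. The documents do not support this. The intervention question uses prospective crashes after training, and residence and licence history before entry should balance across the randomised arms in expectation.

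**Conclusion.** The point holds for the retrospective crash analysis only. The article fixes a single-state source and a uniform 5-year window, while eligibility and the exposure items leave most of that window unsecured and unmeasured. Crash rates from the look-back may therefore be too low, and associations with cognition may be distorted if incomplete observation is related to cognition. The amount cannot be calculated from the document. The 5-15% figure assumes that 10-30% of participants are observable for half the window, that crash rates are constant and equal across participants, and that a 5-year denominator is used. Wider assumptions give 1-24%. The article does not establish that anyone is coded as crash-free, and it does not follow that the randomised comparison is biased.

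**What to change.** Make these changes for the look-back only.

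1. At baseline, record the dates of Alabama residence and of licensure, including any gap, within the previous 5 years.
2. Analyse retrospective crashes per person-year of observable Alabama time, with the log of that time as an offset. Say in advance whether time in Alabama without a licence counts towards it.
3. Add a sensitivity analysis limited to participants with the full 5 years.
4. State that the retrospective rates describe people who were licensed at entry.

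Do not carry the licensed-time restriction into prospective follow-up. Licence loss after randomisation may result from a crash, so censoring there could be informative and would damage a comparison that this issue does not affect.

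The cost is a few extra baseline fields, an offset term, and slightly less person-time. The article reports enrolment as ongoing, so the dates could still be collected when it was written. They may be hard to recover once follow-up has ended.

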To promote successful aging and optimal functioning in the aging HIV population, speed of processing is a preferred target for this cognitive training intervention based on the following points. First, speed of processing is 1 of the most essential neurocognitive abilities that declines with aging, beginning in one’s 40s [69-71]. With HIV considered as a form of accelerated aging [72,73], concerns about more profound speed of processing declines in this population increase. Second, speed of processing declines are related to poorer everyday functioning (eg, driving, performing IADLS) as well as lower quality of life (eg, health-related quality of life) [74]. Third, speed of processing training has been shown to improve this neurocognitive ability [75,76]. Fourth, this improvement in speed of processing has been shown to translate into improved driving performance, mobility, and performance on IADLs [77-83]. Fifth, in community-dwelling older adults, these neurocognitive improvements (ie, using a speed of processing measure called useful field of view) have been shown to be robust over several years; such long-term improvements may also be produced in adults with HIV. Finally, in the ACTIVE study, additional beneficial outcomes have been identified as a result of speed of processing training that include: (1) improved self-rated health [84], internal locus of control [85,86], and health-related quality of life [87-89]; and (2) protection against depression [90]. These outcomes reflect areas that must be addressed in adults with HIV who also may have reduced health-related quality of life [91-93], poor self-rated health [94], decreased locus of control [92,95-97], and depression [45,91,97,98]. These quality of life outcomes are essential areas in HIV that likewise require intervention [99]. This RCT of 264 adults with HAND extends the ability to demonstrate whether speed of processing training can improve speed of processing and everyday functioning not only in the short-term, but also during an extended 2-year period.

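### The 5-year retrospective crash analysis can show neurocognitive correlates of past crashes, not predictors, because cognition is first measured after the crashes

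*Protocol article*

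**What the plan says.** The paragraphs on state crash records in the Results section of the Protocol article describe two uses of the records.

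- **Retrospective.** Once the initial sample's "baseline data are collected", the "driving records can be requested for the 5 years prior to starting our study" and "examined to determine crash rates and neurocognitive predictors of crashes".
- **Prospective.** After training, "it can be determined through logistic regression and hierarchical regression whether this intervention was effective" in reducing the frequency and severity of crashes. This use is described only as a test of the intervention.

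The preceding paragraph uses more cautious language: "these state crash records can be used to determine what variables are correlated to the number of total crashes".

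On the timing of cognitive testing, the same section says: "Study measures are assessed at baseline, immediate posttest following training, and at 2 annual follow-ups". No cognitive measurement before baseline is described. Under Inclusion Criteria, "participants must be licensed drivers when entering the study".

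**The concern.** A statement about predictors normally implies that the predictor was observed before the outcome. In the retrospective analysis the order of observation is reversed: the crashes come first and the cognitive score afterwards. Three features of the design make this more than a formality.

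1. The section Rationale of Speed of Processing Training calls speed of processing one of the "most essential neurocognitive abilities that declines with aging", from the 40s onward, and expresses greater concern about decline in HIV. Participants are aged 40 or over. The baseline score is therefore not the score at the time of an earlier crash.
2. People who died, or who lost or gave up their licence after a crash, cannot enter the sample.
3. The measures that might adjust for how much and where people drove do not cover the crash window.

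At stake is the interpretation of a secondary observational result. The wording matters because the Introduction moves from a cross-sectional simulator finding, described in predictive terms, to the suggestion that improving speed of processing may improve driving. A retrospective result labelled as a set of predictors could be used in the same way.

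**Working it through.** The plan states no figure for this analysis (no crash rate, power or effect size), so there is nothing to reproduce. The check is of temporal order.

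**Step 1: timeline.** Put baseline at year 0. The retrospective window runs from year -5 to year 0, taking the 5 years as counted back from each participant's entry. The first cognitive score is at year 0. A crash at year -u precedes its supposed predictor by u years, with u between 0 and 5. No crash in the window follows the score.

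**Step 2: length of the lag.** The article gives no crash dates, so an assumption is needed. If crashes are spread evenly over the window:
- mean lag = 5 / 2 = 2.5 years;
- share of crashes more than 2 years old at testing = (5 - 2) / 5 = 60%.

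Without that assumption the mean lag could lie anywhere from 0 to 5 years. These figures describe the lag. They do not measure bias.

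**Step 3: coverage of the driving measures.** Driving avoidance is asked about the past 3 months, which is 3 / 60 = 5% of a 60-month window. Driving space is asked about the past year, which is 1 / 5 = 20%. The article notes that exposure and avoidance are assessed at each time point, but that helps only the prospective analysis.

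**Step 4: possible direction of bias.**
- Decline after the crash that is unrelated to the crash acts mainly as measurement error and tends to weaken the association.
- Injury in the crash that lowers the baseline score would strengthen it. Exclusion Criteria removes brain trauma with more than 30 minutes' loss of consciousness, so this route is reduced, but milder injury remains.
- Absence of drivers who are no longer licensed can weaken it.

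These do not all point the same way, and the article gives no figure for any of them. Neither sign nor size can be derived.

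**Step 5: is correctly ordered information available?** Yes. Baseline cognition precedes the crashes in the prospective records, which the trial already plans to obtain. The pre-study crash count is fixed before randomisation.

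**Step 6: price of the shorter window.** If the crash rate were constant (assumption) and the same people were followed, about 2 years would yield 2 / 5 = 40% of the crashes in 5 years. With standard errors roughly proportional to 1 / sqrt(number of crashes), intervals would be about sqrt(5 / 2) = 1.6 times as wide.

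**The case against.** The strongest reply is that this is a matter of vocabulary. The article labels the analysis as retrospective, speaks of correlated variables one paragraph earlier, and makes no explicit causal or forecasting claim. Predictor is also the ordinary regression term for an independent variable, and the Introduction uses predictive language for a study it calls cross-sectional. The retrospective look is optional in its wording, none of the three aims depends on it, and the effect of the intervention on crashes is examined separately. A longer, pre-intervention window is also a defensible choice for an infrequent outcome. Post-baseline crashes are not a perfectly clean alternative either, since training is meant to change the cognition that serves as predictor.

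Most of this stands and limits the weight of the point. It does not remove it: the article names the pre-study window as the source of its predictors, while the correctly ordered records are described only as a test of the intervention.

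A reader might infer more than the document supports in three ways.

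- *That cause follows effect.* This is not shown. The measurement of cognition follows the crashes; the impairment may have been present earlier.
- *That the trial's treatment comparisons are compromised.* They do not use the retrospective association.
- *That leaving the prior crash count out of the prospective model is an error.* A condensed article may leave covariates to the full protocol or analysis plan. Its use is a recommendation here.

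**Conclusion.** The point holds as a limit on interpretation. Relating baseline cognition to crashes in the preceding 5 years yields a retrospective association in people who are still licensed, with a score that is only a proxy for cognition at the time of the crash and with avoidance and driving-space items covering at most the past year. It cannot support a statement that cognition predicts crashes.

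This rests on the stated assessment schedule and crash window alone; the even-spread assumption serves only to illustrate the lag. The importance is low, because no randomised comparison changes. It is still worth correcting, because data in the right order are already planned.

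**What to change.** 1. Keep the 5-year retrospective analysis, but report it as neurocognitive correlates of past crashes.
2. Base any statement about predictors on baseline cognition against crashes after baseline, from the prospective records. Include arm, driving exposure, and a check of the arm-by-cognition interaction, because training may change what a baseline score means for later crashes.
3. Use the 5-year pre-study crash count as a baseline covariate in the prospective crash model.

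No new data collection is needed; the change is to wording and model specification. The downside is fewer crashes in the roughly 2-year window, hence wider predictor estimates. The article gives no crash rate, so the exact loss cannot be computed. The interaction check will be imprecise for the same reason and should be read as a check, not as a test with known power.

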### Overview of Overall Study Design

A pre-post 3-group experimental longitudinal design is used (Figure 1). Participants with HAND are administered a neurocognitive, functional, and quality of life assessment battery at baseline, approximately 11-12 weeks postintervention and annually for up to 2 years. This translational science study recruits adults 40+ years with HAND and assigns them to 1 of 3 groups: (1) 10 hours of speed of processing training, (2) 20 hours of speed of processing training, and (3) 10 hours of Internet navigation training (ie, a contact-control condition).

Recruitment flyers are posted at a university HIV and acquired immunodeficiency syndrome (AIDS) clinic targeting those 40+ years only. Interested potential participants call the study telephone number to be told more about the study and to determine if they meet basic eligibility requirements (eg, HIV+, 40+ years); if they do, they are scheduled for a baseline assessment appointment. During this appointment, participants are consented and administered a neurocognitive, everyday functioning, and quality of life assessment. From this assessment, a HAND diagnosis is determined. Based on prior prevalence rates, it is expected over half of the participants experience HAND; only those with HAND and thus who need such a cognitive intervention are randomly assigned to 1 of the 3 treatment arms. Block stratified random assignment will minimize the risk of imbalance among randomized groups in 2 key factors: minority status and speed of processing deficiency measured by a cut off using the useful field of view test [100]. Completion of each arm should take participants approximately 10 weeks. After training, participants are administered the same baseline assessment at posttest and then annually for 2 years. Two years of follow-up is justified because it is needed to determine the robustness of the speed of processing training over time in this clinical population as observed in the older adults in the ACTIVE study. To retain participants over a 2-year period, several strategies are employed; here are a few examples: (1) sending reminder holiday and birthday cards to participants; (2) providing little gifts to participants with the study name, phone number, and logo on them; and (3) gathering information on secondary contacts of people they know so we can track them down in case such participants move. In addition, participants are compensated for their time they spend with the study.

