In the contact-control group, participants receive 10 hours of Internet navigation training; it has been used successfully as an optimal social or computer contact-control condition for speed of processing training studies. This contact-control (sham) condition mirrors speed of processing training with the same amount of social contact with study staff and computer exposure, but does not provide any therapeutic neurocognitive benefit as we have previously observed [75,81,109]. Specifically, participants are given instructional materials and exercises on how to navigate the Internet. For more computer savvy participants, they are directed to other websites that may be of interest. These Internet activities reflect those which people do normally and do not have any observable neurocognitive therapeutic effect. This approach has been used in prior National Institute on Aging-sponsored studies [75]. This contact-control group is being used to compare with the other intervention in which only 10 hours of the speed of processing training are being provided; this will allow for a direct comparison. Meanwhile, the intervention with 20 hours of training is being included to test whether the extra dosage will be more effective versus 10 hours of speed of processing training alone.

Finally, a treatment fidelity checklist is used so staff can review with participants the amount of time that they have engaged in training. Furthermore, the POSIT Science software monitors the amount of time participants spend engaged in each exercise. As in the ACTIVE study, participants are considered to be trained when they successfully complete 80% of the training [107]. This completer-only analysis is appropriate for use when examining the actual potential of the speed of processing training. If participants do not complete training, their data can be examined using an intent-to-treat analysis.

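### The article says the trial can determine whether training reduces crashes and relies on a large sample, but 264 participants in three arms over about 2 years cannot settle that for an infrequent event

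*Protocol article*

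**What the plan says.** The statements are in the Protocol article, Results, in the paragraphs on state crash records.

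- On what the analysis will deliver: "it can be determined through logistic regression and hierarchical regression whether this intervention was effective in reducing the frequency and severity of vehicle crashes".
- On sample size: "Given the infrequent nature of vehicular crashes, the large sample size of this study will provide insight into whether this intervention is effective".
- On when the prospective analysis is done: "Prospectively, once participants have completed the training in our 2-year study".

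Crash outcomes are described there as numbers of total, at-fault and not-at-fault crashes. Records are requested from the state by driver's licence number, and a 5-year pre-study record is also to be obtained. Driving exposure and avoidance are measured at each visit, and their influence on crash risk may be examined.

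The design facts are elsewhere. Rationale of Speed of Processing Training gives the size: "This RCT of 264 adults with HAND". Overview of Overall Study Design says the trial "assigns them to 1 of 3 groups" and assesses participants "annually for up to 2 years". Intervention Dosage Versus Control Condition names 10 hours of training against the contact control as the direct comparison.

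**The concern.** The text makes a positive claim about what the design can show. Rarity counts against that claim: information on a rare event comes from the number of events, and 264 people split three ways and followed for about 2 years produce few. Crash records are one of three main ways in which driving is assessed, and driving is presented as a primary and novel focus, so the claim matters.

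The named models are a second problem. The stated target includes the frequency of crashes, and the outcomes are counts. Neither model, as named, is a model for a rate.

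If the wording stands, a null crash result could be taken as showing no driving-safety benefit when the data could not have shown one. A chance difference on very few events could likewise be given too much weight.

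**Working it through.** The article attaches no power, target effect or crash rate to this outcome, so there is no figure of its own to reproduce. The check is a sensitivity range.

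**Inputs from the article:** N = 264; three arms; about 2 years of follow-up.

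**Assumptions:** equal allocation, 264 / 3 = 88 per arm; no loss of records; control rates of 3%, 5% and 10% per person-year; a rate ratio of 0.5, which is an optimistic effect; two-sided 0.05; Poisson counts.

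**Expected crashes.** Control crashes c = 88 × 2 × rate. With the rate halved, one trained arm expects c/2, and the two trained arms together expect 2 × c/2 = c.

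| Control rate per person-year | Control | One trained arm | Both trained arms |
|---|---|---|---|
| 3% | 5.3 | 2.6 | 5.3 |
| 5% | 8.8 | 4.4 | 8.8 |
| 10% | 17.6 | 8.8 | 17.6 |

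**Power, exact test.** Given the total number of crashes, the trained count is binomial. With no effect, its probability is 1/2 (one arm v control) or 2/3 (pooled v control). Summing over the Poisson distribution of the total gives:

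| Control rate per person-year | One arm v control | Pooled v control |
|---|---|---|
| 3% | 8% | 17% |
| 5% | 15% | 27% |
| 10% | 33% | 51% |

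**Precision with no true effect.** The 95% interval for the pooled rate ratio extends by a factor of exp(1.96 × √(1/c + 1/(2c))) either way:

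- c = 5.28: about 2.8
- c = 8.8: about 2.2
- c = 17.6: about 1.8

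Even at the highest rate, a null estimate of 1.0 would have an interval of about 0.56 to 1.8 (1/1.77 to 1.77), so a sizeable benefit or harm would remain possible.

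**Check with a Wald test of the log rate ratio.** SE = √(1/e₁ + 1/e₂), where e₁ and e₂ are the expected crashes in the two groups. At 0.10 and 0.20 crashes per person over 2 years (5% and 10% per year), power is 22% and 39% for one arm and 31% and 54% pooled. This is somewhat higher than the exact test, with the same conclusion.

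**Check as any crash v none.** This is the question logistic regression answers. The test is of two proportions, with risk halved and 88 per arm:

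| 2-year control risk | One arm v control | Pooled v control | N per arm for 80% power |
|---|---|---|---|
| 5% | 14% | 21% | 906 |
| 10% | 24% | 35% | 435 |
| 20% | 46% | 61% | 199 |

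Reaching 80% power for a halved risk would need a 2-year control risk of about 38% (one arm) or 30% (pooled). A risk that high does not fit an event described as infrequent. With a risk ratio of 0.7, one-arm power is 7%, 11% and 18% at risks of 5%, 10% and 20%.

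At-fault crashes are a subset of all crashes, so at the same rate ratio their power is lower. The same holds for any analysis restricted to severe crashes.

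**The named models.** A person with three crashes and a person with one are the same to a logistic model, so it cannot estimate a change in frequency. Hierarchical regression may mean predictors entered in blocks or a multilevel model, and the article gives no outcome distribution for either.

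**The case against.** The strongest reply is that the article promises only insight from the sample size, that crash records support the other driving measures, and that 264 is large beside the earlier HIV studies it cites (46 and 26 participants). That is fair about the word insight. It does not cover the adjacent sentence, which says effectiveness in reducing crashes can be determined.

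Some stronger readings are tempting, but the documents do not support them.

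- **Only a handful of crashes per arm.** A reader might state this as fact. No rate is given, and at 10% per person-year the control arm expects about 18. The conclusion does not depend on it.
- **The models misuse count data, with wrong linear standard errors.** The article never says the hierarchical regression is linear; it could have a count or binary link. Logistic regression is valid for any crash v none. The supportable point is narrower: neither method is identified as a rate model.
- **The crash analysis excludes non-completers.** The clause on completed training parallels the preceding one on when the retrospective analysis is done, so it most naturally sets timing. The intervention section does endorse a completer-only analysis, with intent-to-treat as an option, so a clarification is worthwhile. No sentence applies that restriction to crashes.
- **The pre-study crash count is wrongly left out of the treatment comparison.** Covariates are routinely left to the analysis plan, so silence here is no fault.

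It is also true that a count model does not cure the low power: the main power figures above already assume one. The model change makes the estimate answer the stated question; the change in wording deals with the power.

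**Conclusion.** The claim that the trial can determine an effect on crash frequency and severity is not supportable, and the sample is not large for this outcome. For a halved rate, power is about 8% to 33% for one trained arm against control and 17% to 51% for both pooled, over assumed rates of 3% to 10% per person-year. The figures rest on equal allocation, about 2 years of complete records and a halving of the rate. Losses or a smaller effect would lower them. The conclusion would fail only if roughly 30% to 40% of controls crashed within 2 years.

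On the models, the finding is limited: logistic regression drops repeat crashes and so does not address frequency, and hierarchical regression is left undefined for a count. The absence of a power calculation from the article is not part of the finding. The point should be corrected; it concerns one of several everyday-functioning outcomes and does not affect the others.

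**What to change.** 1. Replace the statements that effectiveness can be determined and that the sample is large. Say that the crash analysis is exploratory and that absence of a difference is not evidence of no effect.
2. Estimate rate ratios with 95% confidence intervals from a Poisson or negative binomial model with a log person-time offset, and use the 5-year pre-study crash count as a covariate.
3. Include all randomised participants. State that the clause on completing training sets timing and excludes no one; because records are requested by licence number, leaving training or study visits need not end crash follow-up.
4. Keep 10 hours v control as the direct comparison. Add both trained arms pooled v control as a more precise estimate.
5. Report total and at-fault crashes separately. Treat severity as descriptive, since a rate model does not address it.

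The records are already to be requested and the model is standard, so the cost is some wording and a little analysis work. The downside for the sponsor is a less favourable claim about driving safety.
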